The safety termination criteria are: ischemic ECG changes, severe arrhythmias, or abnormal blood pressure (systolic ≥220 mmHg or diastolic ≥110 mmHg). The effort/quality reference criteria (which do not trigger immediate termination) include: respiratory exchange ratio (RER) ≥1.10, heart rate ≥85% of predicted maximum, or appearance of a VO_2_ plateau. The predicted maximum heart rate will be calculated using the formula: HRmax = 220 − age. For patients taking beta-blockers, or those with atrial fibrillation, or post-stroke autonomic dysfunction, the 85% predicted heart rate criterion may not be applicable; in such cases, effort adequacy will be assessed based on a combination of VO_2_ plateau, RER, and the reason for termination, rather than relying on a single heart-rate criterion. Inability to maintain pedaling rate is also a termination indicator. After test termination, the reason for termination will be recorded according to the following classification: cardiopulmonary limitation, neurological or motor limitation, musculoskeletal limitation, safety-related termination, or technical failure. The primary outcome is VO_2_peak, calculated as the average value over the final 30 s before termination. Gas and flow sensors will be calibrated before each test. Data will be acquired and stored using the dedicated SpiroPerfect cardiopulmonary exercise testing software.

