VO_2_peak will be reported both as an absolute value (L/min) and relative to body weight (mL/kg/min). For tests terminated prematurely due to symptoms, the average VO_2_ over the final 30 s before termination will be taken as VO_2_peak, and the reason for termination will be recorded. Invalid tests due to non-physiological reasons will be repeated within 48 h. The proportion of participants meeting the criteria for adequate effort, peak work rate, exercise duration, and the reason for termination will be reported to comprehensively assess test quality. The ventilatory threshold will be analyzed as an exploratory outcome when data permit. Adequate effort will be determined based on a combination of VO_2_ plateau, respiratory exchange ratio, heart rate response (≥85% predicted), exercise duration, and the reason for termination, to avoid misclassifying effort as insufficient based on a single criterion (e.g., RER < 1.05). The primary analysis will follow the intention-to-treat principle, with missing data handled using multiple imputation. In the per-protocol analysis, participants who fail to achieve maximal effort (respiratory exchange ratio <1.05 or heart rate <85% of predicted) will be excluded as a sensitivity analysis.

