### Statistical methods

Statistical analyses will be performed using SPSS 26.0 and R 4.1.0, following the intention-to-treat principle. All tests will be two-sided, with a significance level of *α* = 0.05 unless otherwise specified for multiple comparisons. Statisticians will remain blinded to group allocation until data lock. All randomized participants will be retained in the intention-to-treat analysis. The per-protocol analysis will report the proportion and characteristics of participants who do not meet the effort criteria. Additional stratified analyses will be considered: (1) all randomized participants; (2) those meeting adequate-effort criteria; (3) those terminating due to cardiopulmonary limitation; and (4) those terminating due to neurological or motor limitation, to assess the robustness of the results. For the primary outcome, VO_2_peak will be analyzed using a linear mixed-effects model, with group, time, and their interaction as fixed effects and participant as a random effect (random intercept) to account for within-subject correlations; a random slope may be added if model fitting requires. Age, sex, baseline VO_2_peak, stroke type, disease duration, baseline National Institutes of Health Stroke Scale score, and recruitment source (hospital or community) will be included as prespecified covariates. In the model, the time factor (T0, T1, T2) is used to estimate longitudinal trends, while baseline VO_2_peak is included solely as a covariate to adjust for baseline differences; the two serve different functions and do not constitute redundant adjustment. The covariance structure will be selected from unstructured, compound symmetry, or first-order autoregressive models based on the Akaike information criterion or Bayesian information criterion. The primary treatment effect will be assessed based on the baseline-adjusted between-group difference in VO_2_peak at T1, and the effect estimate, 95% confidence interval, and corresponding *p*-value will be reported. For secondary outcomes, all four measures (interleukin-6, tumor necrosis factor-alpha, National Institutes of Health Stroke Scale, and modified Barthel Index) will be analyzed longitudinally using the same linear mixed-effects model as for the primary outcome. For variables with substantial deviation from normal distribution or violations of parametric assumptions, generalized linear mixed models or nonparametric methods will be used as supplements. To control for multiple comparisons, a Bonferroni correction will be applied for the four secondary outcomes, with the significance threshold set at *α* = 0.05/4 = 0.0125. The exploratory outcome (heart rate variability) will not be adjusted for multiple comparisons and will be used only for exploratory interpretation. For missing data, the primary analysis will use the linear mixed-effects model under the missing-at-random assumption, utilizing all available observed values. To assess robustness, multiple imputation by chained equations and per-protocol analysis will be conducted as sensitivity analyses. In addition, the originally prespecified repeated-measures analysis of variance will be performed as a complementary analysis for comparison with the primary results; if the sphericity assumption is violated, the Greenhouse-Geisser correction will be applied, and *post-hoc* comparisons will be performed using the Bonferroni method. The incidence of adverse events will be compared using Fisher's exact test. If the sample size permits, prespecified exploratory subgroup analyses will be conducted for stroke type (ischemic vs. hemorrhagic) and recruitment source (hospital vs. community), using interaction tests to assess potential effect modification, with results interpreted only as exploratory. Due to sample size constraints (80 participants per group), stratification was performed only for age and disease duration. Other heterogeneity factors, including stroke type, baseline NIHSS score, and baseline VO_2_peak, have been incorporated as prespecified covariates into the linear mixed-effects model for adjustment.

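### The per-protocol effort exclusion removes participants on a single failed criterion, against the protocol's own composite definition of effort, and neither it nor the effort and termination strata name the visit that defines them

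*Protocol article*

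**What the plan says.** All of this is in the protocol article.

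- **Reference criteria** (Cardiopulmonary exercise testing). Good effort is indicated by "respiratory exchange ratio (RER) ≥1.10, heart rate ≥85% of predicted maximum, or appearance of a VO_2_ plateau".
- **Heart-rate waiver** (same section). With beta-blockers, atrial fibrillation or post-stroke autonomic dysfunction, "the 85% predicted heart rate criterion may not be applicable". Effort is then judged on plateau, RER and reason for termination, "rather than relying on a single heart-rate criterion".
- **Composite definition** (same section). "Adequate effort will be determined based on a combination of VO_2_ plateau, respiratory exchange ratio, heart rate response (≥85% predicted), exercise duration". A fifth element is why the test stopped. The stated purpose is "to avoid misclassifying effort as insufficient based on a single criterion (e.g., RER < 1.05").
- **Per-protocol exclusion** (same section, two sentences later). "In the per-protocol analysis, participants who fail to achieve maximal effort (respiratory exchange ratio <1.05 or heart rate <85% of predicted) will be excluded". This is labelled a sensitivity analysis.
- **Strata** (Statistical methods). Analyses that will be considered include all randomised participants, those with adequate effort, and "those terminating due to cardiopulmonary limitation; and (4) those terminating due to neurological or motor limitation". Their stated purpose is to assess robustness.
- **Primary time point** (Primary outcome measure). T1, the end of the intervention.

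No visit is named for the exclusion or for the strata.

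**The concern.** There are two separate problems.

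The first is a contradiction in the text. The composite definition exists to stop one criterion from classing a test as inadequate, and its example is RER below 1.05. The exclusion rule then makes that same RER value sufficient to drop a participant, and heart rate below 85% sufficient as well. It does not carry over the waiver. That omission matters in this population: the Discussion describes autonomic imbalance as frequent after stroke, and Data collection allows beta-blockers at stable doses. (The atrial fibrillation part of the waiver is largely moot, because atrial fibrillation is an exclusion criterion.)

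The second is conditional. VO2peak, RER, peak heart rate and termination reason all come from the same test. If the T1 or T2 test defines who is kept, membership is a post-randomisation result. The Introduction names cardiac chronotropic function as a possible route of action for taVNS, so an effect on peak heart rate is plausible. Selection could then differ by arm, and agreement or disagreement with the primary result could arise from selection alone.

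**Working it through.** The protocol gives no failure rates and no heart-rate distribution, so it has no figure to reproduce. Step 1 uses the text only. Steps 2 to 4 are illustrations on stated assumptions.

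**1. The rules side by side**

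| Question | Composite definition and waiver | Per-protocol exclusion |
|---|---|---|
| Elements used | Plateau, RER, heart rate, duration, termination reason | RER, heart rate |
| Can one failure decide? | No | Yes, either one |
| Heart-rate waiver? | Yes | No |
| Visit named? | No | No |

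Take a participant on a beta-blocker with a VO2 plateau, RER 1.12 and peak heart rate 78% of predicted. The reference criteria and the waiver support adequate effort. The exclusion rule drops this participant.

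**2. How many an either-criterion rule can remove**

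Let p be the RER failure rate and q the heart-rate failure rate. With independent failures the share excluded is 1 - (1 - p)(1 - q). Whatever the dependence, it lies between max(p, q) and p + q.

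- p = 0.20, q = 0.40: 1 - 0.80 × 0.60 = 0.52. Of the 128 evaluable participants planned, 128 × 0.48 = 61 remain.
- p from 0.10 to 0.40 and q from 0.20 to 0.60: 28% to 76% excluded, leaving 92 down to 30 of 128.
- Requiring both failures would exclude p × q, which is 2% to 24% over the same range.

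**3. Selection error if the T1 test defines the set (heart-rate limb only)**

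Assume no true effect on VO2peak, peak heart rate in the sham arm with mean 82% of predicted and SD 10, and correlation r = 0.4 between peak heart rate and VO2peak. For an arm with mean m, let a = (85 - m)/10. The share kept is 1 - Φ(a). The mean VO2peak among those kept, in SD units, is r × λ(a), where λ(a) = φ(a)/(1 - Φ(a)). For sham, a = 0.3, 38.2% are kept, λ = 0.998 and the mean is 0.399.

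| Shift in peak heart rate with taVNS (points) | a | Kept, active | λ(a) | Active minus sham (SD) |
|---|---|---|---|---|
| +5 | -0.2 | 57.9% | 0.675 | -0.13 |
| +3 | 0.0 | 50.0% | 0.798 | -0.08 |
| 0 | 0.3 | 38.2% | 0.998 | 0 |
| -3 | 0.6 | 27.4% | 1.215 | +0.09 |
| -5 | 0.8 | 21.2% | 1.367 | +0.15 |

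For example, at +5: 0.4 × (0.675 - 0.998) = -0.13. Varying the sham mean from 78% to 90% gives +0.07 to +0.16 SD for shifts of -3 to -5, and -0.06 to -0.14 SD for shifts of +3 to +5. The share of sham excluded by this limb alone runs from 76% (mean 78%) to 31% (mean 90%).

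**4. Both limbs together**

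A simulation with 2,000,000 participants per arm assumed failure rates in sham of 20% (RER) and 40% (heart rate), a correlation of heart rate with fitness of 0.3 to 0.6, and of RER with fitness of 0.3. If treatment raises peak heart rate by 0.25 to 0.5 SD, a true null appears as -0.04 to -0.15 SD among those kept, and a true effect of 0.50 SD appears as 0.46 to 0.35 SD. With no treatment effect on heart rate or RER the error is zero.

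**The case against.** **The effect on the trial is limited.** The primary analysis is intention-to-treat with all randomised participants, per-protocol is labelled a sensitivity analysis, and the strata are only to be considered. The protocol will also report the proportion and characteristics of those who miss the effort criteria. All of this stands and bounds the severity. It does not remove the contradiction, because the exclusion rule and its cut-offs are stated in the article.

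**The visit may be left to a fuller document.** An article can leave that detail out. The silence counts here only because the choice decides whether these analyses are comparisons on baseline data or on post-randomisation results. If T0 is intended, the selection problem disappears.

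**Maximal effort may differ from adequate effort.** The exclusion sentence uses the first term and the composite definition the second. The article gives no separate definition of maximal effort, and Statistical methods describes the per-protocol analysis simply in terms of the effort criteria. The distinction does not rescue the rule.

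Three stronger readings are tempting, and the documents do not support them:

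- *That the plan certainly selects on post-randomisation results.* No visit is stated, and bias also needs a treatment effect on the selection variables.
- *That the rule would manufacture a benefit for taVNS.* That sign needs a fall in peak heart rate. Improved chronotropic function more naturally suggests a rise, which would bias against taVNS.
- *That RER 1.10 and RER 1.05 are conflicting cut-offs.* The first supports good effort and the second marks failure. Two thresholds with different roles need not conflict.

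**Conclusion.** The contradiction holds on the text alone: the per-protocol exclusion applies a single-criterion rule that the same section says it wants to avoid, and it drops the heart-rate waiver. How many participants it would misplace cannot be known from the documents. The exclusion rates worked out above depend entirely on assumed failure rates.

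The selection point holds conditionally. If T1 or T2 tests define the sets and taVNS changes peak heart rate, the restricted comparisons carry an error that could go either way. Its illustrative size is about -0.13 to +0.15 SD for shifts of +5 to -5 points, with a mean of 82% of predicted, SD 10 and correlation 0.4. For scale, the sample size section plans on f = 0.25, which by its own f = d/2 is d = 0.50. An error of this order would blur a robustness check without overturning it.

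The correction should be made before enrolment. The primary estimate is not at risk.

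**What to change.** 1. Replace the exclusion on RER or heart rate alone with the composite effort definition, including the heart-rate waiver. State how its five elements combine, which the article leaves open, and use that one definition wherever effort is classified in Cardiopulmonary exercise testing and Statistical methods. The choice of combination is the sponsor's.
2. Define both the per-protocol effort exclusion and the effort and termination strata by the T0 test.
3. Report effort and termination reasons at T1 and T2 by arm, descriptively. If a T1-based subset is kept, label it non-randomised and descriptive, not a test of robustness.

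The cost is wording. Effort data and termination reasons are already recorded at each test, and by the protocol's own account enrolment had not begun when the design was last changed. The downside is that sets defined at T0 cannot show whether the VO2peak measured at T1 was limited by effort. The descriptive T1 report covers that question.

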### Discontinuation and withdrawal criteria

Participants will discontinue treatment or be withdrawn from the study if any of the following occur:
(1)Occurrence of a serious adverse event that, in the investigator's judgment, makes continued participation inappropriate. Such participants will discontinue treatment, but their available data will still be included in the intention-to-treat analysis;(2)Participant voluntarily withdraws informed consent and requests withdrawal. Such participants will be withdrawn from the study, and all data collection will cease;(3)Poor adherence: The actual number of completed intervention sessions is less than 80% of the planned number. Such participants will discontinue treatment but will still be encouraged to continue participating in subsequent follow-up assessments, and their data will be included in the intention-to-treat analysis;(4)Receipt of other interventions during the study period that may affect the outcome measures. Such participants will discontinue treatment, but their available data will still be included in the intention-to-treat analysis;(5)Loss to follow-up (missed two consecutive scheduled visits or unable to be contacted). Such participants will not be considered as having actively withdrawn from the study; their available data will be included in the intention-to-treat analysis, and missing data will be handled using multiple imputation.

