### Intervention

A transcutaneous auricular vagus nerve stimulation device manufactured by Jiangxi Jingyi Medical Technology Co., Ltd., China, will be used. Stimulation electrodes will be placed over the vagus nerve distribution hotspot in the left auricular concha (23, 24). The stimulation parameters are: biphasic square wave, frequency 25 Hz, pulse width 200 µs, single session duration 30 min (25). The stimulation intensity will be individually adjusted based on each participant's sensory threshold. The sensory threshold is defined as the minimum current intensity at which the participant first clearly perceives a tingling sensation on the skin surface (starting from 0.1 mA and increasing slowly). The stimulation intensity in the active taVNS group will be set at a level that is just at or slightly above the sensory threshold (i.e., an intensity that the participant can clearly perceive without pain), typically between 0.5 and 1.5 mA, to ensure a clear, comfortable, and non-painful stimulation sensation. Treatment will be administered once daily, five days per week, for a total of 4 weeks. The sham stimulation group will use the same device, electrode placement, and operational procedures as the active stimulation group. Consistent with previous studies (25), the stimulation current will be set to 0 mA throughout the entire 30 min session. The indicator lights and buzzer sounds of the device will be synchronized with those of the active stimulation group throughout the treatment period.

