### Quality control and assurance

All research personnel will receive unified training before the trial commences. The inter-rater reliability, assessed by the intraclass correlation coefficient for scale assessments, must reach ≥0.85 before personnel can participate in formal evaluations. Data entry will employ a double-entry verification mechanism. The research coordinator will be responsible for ongoing data monitoring and review, conducting monthly data integrity checks. At least three neurology and cardiology specialists will jointly supervise the enrollment assessment and diagnostic process. To protect participant privacy, only the research team members, ethics committee, and relevant regulatory authorities will have access to participants' personal information and medical records.

Adherence monitoring: Adherence to rehabilitation training will be monitored using the same threshold as for taVNS/sham stimulation (≥80% of planned sessions), and will be recorded separately from the intervention adherence.

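### The only stated per-protocol exclusion is an either/or effort rule that conflicts with the protocol's own combined effort definition and leaves treatment received unexamined

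*Protocol article*

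**What the plan says.** The per-protocol rule is in the protocol article under Cardiopulmonary exercise testing: "In the per-protocol analysis, participants who fail to achieve maximal effort (respiratory exchange ratio <1.05 or heart rate <85% of predicted) will be excluded". Statistical methods returns to this analysis and again mentions only effort: "The per-protocol analysis will report the proportion and characteristics of participants who do not meet the effort criteria". The same section gives its purpose: "multiple imputation by chained equations and per-protocol analysis will be conducted as sensitivity analyses".

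Adherence is handled elsewhere. Discontinuation and withdrawal criteria, item (3), describes poor adherence as follows: "The actual number of completed intervention sessions is less than 80% of the planned number". Treatment stops for these participants, follow-up is encouraged, and "their data will be included in the intention-to-treat analysis". Item (4) gives participants who receive other outcome-affecting interventions a similar intention-to-treat statement. Neither item mentions the per-protocol set.

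On effort, Cardiopulmonary exercise testing says two further things. Adequacy is to be judged on plateau, RER, heart-rate response, test duration and the reason for stopping, taken together, so that a single value does not misclassify a test; an RER below 1.05 is its own example. For participants on beta-blockers, with atrial fibrillation or with autonomic dysfunction, the 85% heart-rate criterion may not apply, and the other indicators are to be used.

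**The concern.** A per-protocol analysis is normally read as the effect in those who received treatment as planned. Here the only stated exclusion concerns performance at the outcome test. Three problems follow.

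- The rule excludes on one failed value, which the protocol's own effort definition sets out to avoid.
- Nothing stated uses the session threshold or the co-intervention criterion, although both are already defined, so the analysis says nothing about treatment received.
- At T1 and T2, effort is observed after randomisation, in the test that yields the primary endpoint. The Introduction expects taVNS to change chronotropic function, so a heart-rate exclusion selects on something treatment may alter. Active stimulation is set to be felt while sham is 0 mA, and the blinding section itself raises expectancy effects on CPET performance. The two arms could therefore be filtered differently.

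At stake is the value of one of the two named robustness checks.

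**Working it through.** The protocol gives no figure for the per-protocol set, so there is none to reproduce. The check compares the statements and then illustrates the size.

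**1. Session threshold.** Intervention: "Treatment will be administered once daily, five days per week, for a total of 4 weeks". Planned sessions = 5 × 4 = 20, and 0.80 × 20 = 16. Poor adherence therefore means fewer than 16 sessions.

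**2. Logic of the effort rule.** Exclusion if RER <1.05 *or* heart rate <85% of predicted means that staying in requires *both* RER ≥1.05 and heart rate ≥85%. Under the combined definition, a low heart rate can be outweighed by a plateau, RER and the reason for stopping. The two definitions classify the same test differently.

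**3. Two hypothetical participants aged 60.** Predicted maximum heart rate = 220 − 60 = 160; 85% of this is 136 bpm.
- A: 20 of 20 sessions, on a beta-blocker, RER 1.10, VO2 plateau, peak heart rate 135 (135/160 = 84.4%). The per-protocol rule excludes A. The beta-blocker provision would not judge A on heart rate.
- B: 2 of 20 sessions, RER 1.05, peak heart rate 136. No stated per-protocol criterion excludes B.

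**4. Illustrative size.** Input from the protocol: 80 per arm. Assumptions not in the protocol: inadequate effort (e) of 20-50%, non-adherence (a) of 5-20%, independent of each other.
- Kept by the effort rule alone: 80 × (1 − e) = 64 to 40 per arm.
- Of those, below 16 sessions: 80 × (1 − e) × a. Lowest 40 × 0.05 = 2.0; highest 64 × 0.20 = 12.8.
- Adherent participants dropped: 80 × e × (1 − a). Lowest 80 × 0.20 × 0.80 = 12.8; highest 80 × 0.50 × 0.95 = 38.0.
- Kept by a set based on at least 16 sessions: 80 × (1 − a) = 76 to 64 per arm.

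**5. Illustrative dilution.** Assume further that participants below 16 sessions gain nothing. The estimate in the effort-based set is then (1 − a) times the effect in adherers, a factor of 0.95 to 0.80. Take d = 0.50 in adherers (the sample-size section uses f = d/2 with f = 0.25). At 10% and 20% non-adherence this becomes 0.50 × 0.90 = 0.45 and 0.50 × 0.80 = 0.40. Under independence the share of non-adherers is the same as in the full randomised set, so the effort-based set is no sharper on adherence than intention-to-treat.

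**The case against.** The strongest reply is that the article never says effort is the *sole* criterion. The quoted sentence describes its exclusion as a sensitivity analysis, and the one in Statistical methods says what will be reported, not who is in the set. Naming only intention-to-treat for poor adherers is compatible with leaving them out of the per-protocol set. Full membership rules are often left to the SAP. This stands: a reader might infer that participants with few sessions are certain to be kept, and the text does not establish that. It does not rescue the rule that *is* stated, because a SAP that added adherence would still inherit an either/or effort criterion at odds with the combined definition.

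The beta-blocker provision could be read as overriding the heart-rate half of the rule. That is possible, but the per-protocol sentence makes no exception, and the provision does nothing for other participants excluded on one value.

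Three stronger readings are tempting and are not supported.
- That the two 80% statements conflict. They do not. Quality control and assurance applies the threshold to rehabilitation training, "using the same threshold as for taVNS/sham stimulation (≥80% of planned sessions", and records it separately; the discontinuation criterion concerns the stimulation sessions.
- That those kept are untreated. Someone with 15 of 20 sessions is partly treated.
- That the dilution is an estimate. It rests on assumed rates and on zero benefit below the threshold.

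It is also fair to say that session completion is itself post-randomisation and may differ by arm, so a set based on treatment received is not free of selection. Restricting to valid tests is a legitimate sensitivity analysis for an effort-dependent endpoint; it answers a different question from a per-protocol analysis.

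**Conclusion.** The point holds in this form. The one per-protocol exclusion that the protocol states contradicts its own combined effort definition and its caveat on heart rate. No statement ties the 16-session threshold or outcome-affecting co-interventions to the set. As stated, the analysis drops fully adherent participants on a single effort value and is not a check on treatment received. It also selects on a post-randomisation variable that the protocol expects treatment to influence; the direction and size of any resulting bias cannot be derived from the document.

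How many participants are affected depends on effort and adherence rates that the protocol does not give, so the figure of about 13 to 38 adherent participants dropped per arm is only an illustration. The primary intention-to-treat estimate at T1 is unaffected. The change should be made, because this is one of the two named sensitivity analyses, but it does not threaten the main result.

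**What to change.** - Define the per-protocol set by treatment received: at least 80% of planned taVNS/sham sessions (16 of 20) and no outcome-affecting co-intervention, using the definitions already under Discontinuation and withdrawal criteria, items (3) and (4).
- Take the effort exclusion out of that set and report it as a separately labelled sensitivity analysis. Statistical methods already lists participants with adequate effort as the second of its stratified analyses.
- In that analysis, replace the either/or rule with the combined definition, including the provision for participants in whom the heart-rate criterion may not apply, and state which test (T0, T1 or T2) it refers to.
- State that both sets are post-randomisation selections, and report the numbers and reasons for exclusion by arm.

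The cost is wording only. Session completion, co-interventions, effort measures and reasons for termination are already to be recorded, and the sample size and primary analysis do not change.
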